#### 11.1.5 Adverse events based on symptoms and signs

All AEs spontaneously reported by the patient or health care provider (open-ended question from the study personnel "Have you had any health problem since your last visit/last inquiry") or identified by observation will be collected and recorded.

#### 11.1.6 Adverse events based on examinations and tests

The results of protocol-specified laboratory tests and examinations, namely vital signs, ECG, and other safety assessments, will be summarized in the clinical study report. If these parameters suggest abnormalities compared with baseline, they will be reported as AEs only if they meet the criteria for SAEs, are judged by the investigator as clinically significant, or lead to discontinuation of study treatment (other than due to progressive disease).

When an abnormality in a laboratory value, vital sign, ECG, or other safety assessment is reported as an AE, the investigator should use the clinical term rather than the laboratory term whenever possible (e.g., anemia rather than decreased hemoglobin value).

For AEs of abnormalities in hematology, they should be reported specifically as "white blood cell count decreased", "neutrophil count decreased", "anemia", "platelet count decreased", etc., rather than using the AE name "myelosuppression". Reporting of percentage abnormality AEs (such as "neutrophil percentage decreased") is not required.

In case of abnormal liver enzymes, it should be reported by the name "XX enzyme increased/decreased", and ambiguous names such as "transaminases abnormal/increased/decreased" and "liver enzyme abnormal/increased/decreased" should not be used in reporting.

When changes occur in bilirubin-related indicators, "total bilirubin increased/decreased" and/or "direct bilirubin increased/decreased" and/or "indirect bilirubin increased/decreased" should be used in reporting. Ambiguous names such as "bilirubin abnormal/increased/decreased" and "blood bilirubin abnormal/increased/decreased" are not allowed for reporting.

Laboratory abnormalities due to unequivocal progressive disease should not be reported as AEs. Any new or

worsening clinically relevant abnormality in physical examination as compared to the baseline will be reported as an AE.

#### 11.1.7 Hy's law

If subjects show AST or ALT  $\geq 3 \times$  ULN and total bilirubin  $\geq 2 \times$  ULN, it may need to be reported as an SAE.

Cases meeting Hy's law are subject to expedited reporting as per regulatory guidelines. The investigator is responsible for determining whether a subject meets Hy's law immediately. A detailed description of Hy's law and its handling measures are provided in Appendix C.

#### 11.1.8 Progressive disease

Progressive disease and its associated signs and symptoms are considered an exacerbation of the patient's condition, which may be an increase in the severity of the disease under study and/or an increase in the symptoms of the disease.

New lesions of the primary tumor under study or progression of existing metastases are considered progressive disease rather than an AE. Unequivocal progressive disease during the study will not be reported as an AE.

#### 11.1.9 New cancers

A new cancer should be considered an SAE and it usually meets the criteria of "severe". New cancers are those that are not the primary reason for receiving the study treatment and are discovered after a patient is enrolled in this study. New cancers do not include metastases of the primary cancer.

#### 11.1.10 Handling of deaths

All deaths that occur during the study or during the follow-up period after treatment discontinuation should be reported as follows:

- Deaths that are clearly related to progressive disease should be reported to the CRA at monitoring visits and recorded, but should not be reported as SAEs during the study.
- If the death is not clearly caused by the progression of the study disease, the AE resulting in the death should be reported to the CRA as an SAE within 24 h of awareness. The report should contain the evaluation of progressive disease, primary cause of death, and other possible causes of death.
- Deaths of unknown causes should be reported as SAEs within 24 h of the study site's awareness, but every effort should be made to identify the cause of death. An autopsy may be helpful in assessing the cause of death. If an autopsy is performed, a copy of the autopsy results should be reported to the drug marketing authorization holder (Jiangsu Hansoh Pharmaceutical Group Co., Ltd.) within 24 h after the results are available.

#### 11.1.11 Reporting of adverse events

All SAEs, regardless of whether considered causally related to the IMP or study procedures, should be reported. All SAEs will be recorded. The investigator or other site personnel will immediately notify the drug marketing authorization holder (Jiangsu Hansoh Pharmaceutical Group Co., Ltd.) of any SAE that occurs throughout the study (from the time of informed consent to the end of the follow-up period), and no later than 24 h after awareness of the SAE.

For fatal or life-threatening AEs with significant or relevant information missed, subsequent active actions will be taken immediately. The investigator or other personnel at the study site should immediately notify the sponsor and funder of any subsequent information about the SAE in the previous report, no later than 24 h after awareness of the subsequent information about the SAE. The contact information is shown in Table 8.

## 11.2 Overdose

Any subject receiving a higher-than-expected dose of the drug should be closely monitored by the investigator and should receive appropriate supportive care and close follow-up. Overdoses should be documented as follows:

- AEs or symptoms associated with an overdose should be recorded in both the AE section and the overdose section of the medical record.
- An overdose without associated symptoms should only be recorded in the overdose section of the medical

record, i.e., an overdose without discomfort will not be considered an AE and does not need to be recorded in the AE section of the medical record.

If an overdose occurs during the study, the investigator or other personnel at the study site should inform the sponsor and the funder immediately or within 24 h of knowing of the event. Designated representative(s) of the funder will work with the investigators to ensure that all necessary information is recorded in the sponsor's and funder's secure data entry systems.

SAEs related to overdose should be reported according to the SAE reporting procedure. Other conditions associated with overdose must be reported within 30 days of occurrence.

### 11.3 Pregnancy Report

The collection period of pregnancy reports lasts from the first dose to the end of the safety follow-up period.

All pregnancy reports and related outcomes during the clinical trial should be reported to the sponsor and the funder.

The investigator should complete the "Pregnancy Report Form" and submit it to the sponsor and the funder within 24 h of awareness of any pregnancy event.

#### 11.3.1 Pregnancy of female subjects

If a female subject becomes pregnant, the subject should immediately discontinue treatment, and the investigator should report to the sponsor and the funder within 24 h of awareness of the pregnancy. The investigator should follow up the pregnancy outcome until 28 days after delivery and report the outcome to the sponsor and the funder. Pregnancy itself is not considered an AE; only the "Pregnancy Report Form" needs to be completed and submitted to the sponsor and the funder within 24 h. Unless there is any negative pregnancy outcome, such as stillbirth, spontaneous abortion, and fetal malformation, it will be considered an SAE and needs to be reported according to the time requirements for SAEs. An uncomplicated selective abortion will not be considered an AE.

#### 11.3.2 Pregnancy of partners of male subjects

If the partner of a male subject becomes pregnant during the clinical trial, the subject may continue the clinical trial.

The investigator should report to the sponsor and the funder within 24 h of awareness of the partner's pregnancy.

Pregnancy of the partner of a male subject will not be considered an AE. The investigator should follow up the pregnancy outcome of the partner until 28 days after delivery and report the outcome to the sponsor and the funder.

Any negative pregnancy outcome, such as stillbirth, spontaneous abortion, and fetal malformation, is considered an SAE and needs to be reported according to the time requirements for SAEs.

Information regarding pregnancy should not be collected from male subjects, but should be collected from their partners themselves with the informed consent of the partners.

### 11.4 Recommended Toxicity Management

#### 11.4.1 Aumolertinib dose reduction

During toxicity management, aumolertinib dose can be reduced in accordance with the dosages specified in Table 9 below.

**Table 9. Guidelines for dose reduction levels of the investigational medicinal product**

| Aumolertinib                       |                                                  |                                                  |                                                  |
|------------------------------------|--------------------------------------------------|--------------------------------------------------|--------------------------------------------------|
|                                    | Initial therapy                                  | Dose reduction therapy 1                         | Dose reduction therapy 2                         |
| Dose                               | Aumolertinib, 165 mg/day                         | Aumolertinib, 110 mg/day                         | Aumolertinib, 55 mg/day                          |
| Drug                               | Aumolertinib active drug, 55 mg/tablet, 3 tablet | Aumolertinib active drug, 55 mg/tablet, 2 tablet | Aumolertinib active drug, 55 mg/tablet, 1 tablet |
| Dosage and route of administration | p.o., QD                                         | p.o., QD                                         | p.o., QD                                         |

#### 11.4.2 Dose modifications associated with adverse events

If a subject experiences any toxicity of CTCAE Grade  $\geq 3$  and/or any toxicity (any grade) deemed unacceptable by the investigator, which is judged by the investigator to be treatment-related, the study treatment should be interrupted, and supportive care should be provided as needed in accordance with local practices/guidelines. If the toxicity is relieved or returns to  $\leq$  CTCAE Grade 1–2 within 3 weeks after onset, the IMP at the original dose or dose reduction therapy 1 in Table 7 may be given again. If the original dose is resumed, the subject should be closely monitored for 3 days; if the same toxic effect occurs within 3 days, dose reduction therapy 1 should be considered. Decisions should be made in agreement between the investigator and the sponsor.

If the toxicity does not recover to  $\leq$  CTCAE Grade 1–2 within 3 weeks after onset, dose reduction therapy 2 should be considered. If the toxicity still does not recover to  $\leq$  CTCAE Grade 1–2 within 3 weeks or the same toxic effect

occurs within 3 days, the subject should be withdrawn from the study and should be followed up until the toxicity is recovered.

"Treatment-related" herein refers to definitely related, possibly related, and indeterminable, not including unlikely related and not related. Specific dose modification principles are presented in Table 10.

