|                                   | Muscular symptoms # (Grade ≥ 3), with or without CK increased                                                                                              | Interrupt the study treatment for a maximum of 3 weeks*. If the muscular symptoms improve to Grade ≤ 2 within 3 weeks: 
 
Resume the study treatment at the original dose for the first occurrence;
 
Resume the study treatment at one dose level lower if it reoccurs.
 
                                                                                                                                                                                                                                                                       |
| Others                            | Grade ≥ 3 adverse reactions                                                                                                                                           | Interrupt the study treatment for a maximum of 3 weeks*. If the adverse reaction improves to Grade ≤ 2 within 3 weeks: 
 
Resume the study treatment at the original dose for the
 
                                                                                                                                                                                                                                                                                                                                                                     |

|                                                                                                                                                           |  |                                                                                           |
|-----------------------------------------------------------------------------------------------------------------------------------------------------------|--|-------------------------------------------------------------------------------------------|
|                                                                                                                                                           |  | first occurrence;
• Resume the study treatment at one dose level lower if it reoccurs. |

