| At any time, if 55 mg is still intolerable (occurrence of Grade $\geq 3$ adverse reactions), permanent discontinuation of study treatment is recommended. |  |                                                                                           |

Note: The severity mentioned above is graded according to the National Cancer Institute - Common Terminology Criteria for Adverse Events Version 5.0 (NCI-CTCAE 5.0). \* If the study treatment is interrupted for more than 3 weeks and the resumption criteria are not met, the study treatment should be permanently discontinued. # Muscular symptoms (including but not limited to): muscle pain, muscle tenderness, muscle twitching, or muscle weakness. When several AEs occur simultaneously, the dose should be modified according to the most severe AE; once the dose is reduced, it cannot be returned to the previous level. Subjects who discontinue treatment should be observed until the resolution of toxicity; dose interruption does not affect scheduled tumor evaluation. The above decisions should be made in agreement between the investigator and the funder.

For certain patients, if the investigator decides to adopt measures such as continuing treatment without interruption, interrupting treatment, modifying the dose, or permanently discontinuing the study treatment, not in accordance with the dose modification provisions of this section, but based on the benefit/risk considerations, agreement should be reached with the funder.

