#### **12.4.3 Safety analysis**

##### **12.4.3.1 Adverse events**

The AEs that occur from the initiation of treatment until 28 days after the last dose will be summarized in the safety evaluation. The AEs that occur prior to initiation of treatment and AEs that occur after 28 days following the last dose will be tabulated separately and not included in the summary table of AEs.

Treatment-emergent AEs will be summarized by treatment group, mainly including:

- 1) Number and proportion of patients with at least one AE;
- 2) Number and proportion of patients with at least one treatment-related AE;
- 3) Number and proportion of patients with at least one severe (CTCAE Grade  $\geq 3$ ) AE;
- 4) Number and proportion of patients with at least one severe (CTCAE Grade  $\geq 3$ ) treatment-related AE;
- 5) Number and proportion of patients with at least one SAE;
- 6) Number and proportion of patients with AEs resulting in dose modification;
- 7) Number and proportion of patients with AEs resulting in withdrawal;
- 8) Number and proportion of patients with AEs resulting in death.

All AEs will be summarized by SOC and PT. All AEs will be tabulated.

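### Section 11.4.2 gives two incompatible rules for a treatment-related Grade ≥3 toxicity not recovered within 3 weeks: the text lets 55 mg/day be considered, while Table 10 and its note require permanent discontinuation

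*Protocol*

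**What the plan says.** Section 11.4.2 treats the same situation twice.

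- **Running text.** It applies to treatment-related toxicity of Grade 3 or higher, and to any grade the investigator finds unacceptable. Treatment is interrupted. If the toxicity recovers in time, the original dose or the first reduction may be given. If it does not recover "within 3 weeks after onset, dose reduction therapy 2 should be considered". Table 9 defines that step as 55 mg/day. The next sentence opens "If the toxicity still does not recover to" and sets a further 3-week limit, with recurrence within 3 days as the alternative trigger. Only then does it say that "the subject should be withdrawn from the study and should be followed up until the toxicity is recovered". The text closes with "Specific dose modification principles are presented in Table 10".
- **Table 10, row for other Grade ≥3 adverse reactions.** Treatment is interrupted for at most 3 weeks. Resumption is conditional: "If the adverse reaction improves to Grade ≤ 2 within 3 weeks".
- **Table 10 note.** "If the study treatment is interrupted for more than 3 weeks and the resumption criteria are not met, the study treatment should be permanently discontinued".
- **Table 10, last line.** Permanent discontinuation is also recommended in a separate case, which begins "At any time, if 55 mg is still intolerable".

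Both parts require joint decisions. The text names the investigator and the sponsor; the note names the investigator and the funder.

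**The concern.** A patient whose severe drug-related toxicity is still present after 3 weeks meets both rules. Under one, the drug may be restarted at 55 mg/day and the stop decision waits for a second failure. Under the other, treatment is over. A site following the text would believe that it is compliant, and so would a site following the table.

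This is first a patient-safety matter, in a trial that doses at 165 mg/day when 110 mg/day was the dose taken into phase II (Section 4.2.4). It also touches reporting. Section 5.2.2 makes withdrawal due to AEs a safety endpoint. Section 12.4.3.1 plans separate counts for AEs leading to withdrawal and for another category: "Number and proportion of patients with AEs resulting in dose modification". How and when a patient enters these counts may depend on which paragraph was followed. About 20 sites are planned.

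**Working it through.** The plan states no figure to reproduce. The check sets the rules side by side for one case: a treatment-related Grade ≥3 toxicity still at Grade ≥3 after 3 weeks.

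| | Running text, 11.4.2 | Table 10 row and note |
|---|---|---|
| Clock starts at | onset of toxicity | interruption of treatment |
| Not recovered at 3 weeks | consider 55 mg/day | permanent discontinuation |
| Second window | further 3 weeks | none |
| Stop trigger | second non-recovery, or recurrence within 3 days | first non-recovery |

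Three readings might reconcile them.

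1. **Different clocks.** If interruption starts some days after onset, the text's 3 weeks end before the table's. But Table 10 makes resumption depend on improvement to Grade 2 or lower, so giving 55 mg for an unrecovered toxicity breaks it on either clock.
2. **Second paragraph meant only for patients already reduced to 110 mg/day.** The paragraph does not say so. Even if it did, Table 10 would still require discontinuation for non-recovery.
3. **Exception clause at the end of 11.4.2.** This permits departures for certain patients with the funder's agreement. It presupposes a standing rule and cannot say which of two standing rules that is.

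The conflict is not confined to the catch-all row. For CK above 10 × ULN (Grade 4), Table 10 allows resumption one level lower only after improvement to Grade 2 or lower within 3 weeks. The note stops treatment otherwise, yet the text would still have 55 mg considered.

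**Upper bound per patient.** Assume 55 mg/day starts when the first window closes, the second window starts at the same moment, and the toxicity neither recovers nor triggers an earlier stop.

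- Time from onset to stop decision under the text: 3 + 3 = 6 weeks. Under Table 10 it is 3 weeks from interruption.
- Extra doses under the text: 3 × 7 = 21.
- Extra drug: 21 × 55 mg = 1,155 mg. Under Table 10: none.

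**The case against.** Several points weigh against a strong version of this concern.

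- **Central agreement.** Dose decisions need the sponsor's agreement (text) or the funder's (note). This makes uncoordinated divergence between sites less likely, and that point stands. The clauses still do not say which rule the parties should apply, and they name different parties.
- **Permissive wording and a pointer to the table.** Section 11.4 is headed as recommended management, the 55 mg step is only to be considered, and the text refers to Table 10 for specifics. A careful reader may take the table as operative, and a site that considers 55 mg and declines it breaches neither rule. But the text then permits what the table forbids, and no sentence gives the table precedence.
- **Timing of the 55 mg step.** A reader might infer that 55 mg is certain to be given while the toxicity is unresolved. The text does not say when 55 mg starts or when the second window opens, and the 3-day recurrence trigger would fit a restart after recovery. The 21 doses and 6 weeks are therefore a worst case under one reading. A restart after late recovery would still exceed Table 10's 3-week maximum.
- **Effect on reported proportions.** A reader might infer that the safety proportions shift by a calculable amount. The documents give no basis for the number of patients affected. Table 10's dose-modification column itself includes interruption and permanent discontinuation, so on that reading an affected patient counts as having a dose modification under either rule. A patient who fails 55 mg may also end up in the withdrawal count anyway.
- **Loss from follow-up.** A reader might infer that the text's reference to withdrawal from the study ends tumour imaging and harms the primary endpoint. The documents do not support this. Section 7.8.1 lists an adverse event as a reason for treatment discontinuation, and Sections 7.8.1, 9.1.3.3 and 12.1.2 provide for tumour assessment after treatment stops. Section 7.8.2 does not name adverse events, but its list of withdrawal reasons is expressly open. This is loose terminology, worth tidying in the same edit.

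**Conclusion.** The contradiction is real and should be fixed. For a treatment-related Grade ≥3 toxicity not recovered within 3 weeks, the text offers 55 mg/day and a second window, while Table 10 and its note require permanent discontinuation. No reading of the section reconciles the two, and no precedence is stated.

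The consequence is possible further dosing after a severe toxicity has failed to recover, at worst about 3 more weeks under the timing assumption stated, and inconsistent classification of AE-related discontinuations. Confidence is high for the textual conflict itself. How many patients it would reach cannot be estimated from the protocol. Nothing here bears on the sample size, and no effect on the 12-month PFS analysis is claimed.

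**What to change.** 1. Replace the second paragraph of the 11.4.2 text with wording such as: *If a treatment-related Grade ≥3 toxicity does not meet the Table 10 resumption criteria within 3 weeks of interruption, study treatment is permanently discontinued. The subject is followed until the toxicity recovers, and tumour assessments continue until PD. Dose reduction therapy 2 (55 mg/day) is used only as a step-down after recovery.* This also replaces withdrawal from the study with discontinuation of treatment.
2. State that Table 10 governs where text and table differ.
3. In the first paragraph, count the 3 weeks from interruption instead of onset, so that one clock applies throughout. Change the reference from Table 7 (causality criteria) to Table 9 (dose levels).
4. For unacceptable toxicity below Grade 3, which the text covers but Table 10's catch-all row does not, apply the same 3-week limit, with a resumption criterion set by the sponsor's medical team.

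The Table 10 line on intolerance at 55 mg can stay as it is. Following the table is a clinical choice for the sponsor to confirm; it is the more protective of the two rules already in the protocol. The cost is amended wording in one section, one criterion from the medical team and a notice to sites, with no change to sample size, visits or analysis.

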#### 7.5 Procedures for Managing Wrongly Enrolled Subjects

Subjects not meeting the eligibility criteria of the study should not participate in this study. If subjects not meeting the eligibility criteria are enrolled, study treatment should not be provided. If treatment has been started, the investigator should immediately perform a comprehensive assessment and decide whether to discontinue the treatment based on the assessment results. If treatment has been started for a subject not meeting the eligibility criteria, the subject should be withdrawn from the study. This process must be fully documented in the medical record.

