### **7.8 Treatment Discontinuation and Withdrawal from Study**

#### **7.8.1 Treatment discontinuation**

Treatment discontinuation means that the subject no longer receives the study treatment due to the following reasons after the start of study treatment, but is not withdrawn from the study and will complete subsequent follow-ups as scheduled.

1. Progressive disease (refer to 2 in case of free medication)
2. Disease progression after free medication
3. Adverse event
4. Poor compliance

5. Major protocol violation
  6. Patients are no longer eligible to continue with the study treatment as believed by the investigator or funder (e.g., psychiatric disorders or social status that may interfere with subject's rights, safety, cooperation, and participation in this study)
  7. Patients request for treatment discontinuation but agree to continue to be followed up
  8. Patients withdraw the informed consent
  9. Loss to follow-up
  10. Pregnancy
  11. Study termination or site closure
  12. Patients who develop corneal ulcer or interstitial pneumonia should permanently discontinue the treatment
- Every effort should be made to obtain information of patients who discontinue study treatment, including information concerning EOT follow-up and the safety follow-up thereafter. The primary reasons for study treatment discontinuation should be documented on the corresponding eCRF. A patient's request for withdrawal from the study at the same time must be documented in the source documents, with the investigator's signature affixed. In addition, patients who discontinue study treatment due to reasons other than PD should undergo tumor assessments as scheduled until documented PD, unless the patient withdraws from the study due to any of the reasons described in 7.8.2.

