#### **12.1.2 Progression-free survival (PFS)**

According to RECIST 1.1, PFS is defined as the time from the treatment initiation to the first occurrence of investigator-assessed objective tumor progression or death. In the absence of PD, even if the patient has discontinued aumolertinib treatment or received another anti-cancer treatment before PD, his/her imaging tumor evaluation should still be collected until RECIST-defined PD. Symptomatic deterioration is not considered a progression event.

Subjects who have not progressed or died at the time of analysis will be censored at the last date of their last RECIST assessment. If a subject has PD or dies after 2 or more missing visits, he/she will be censored at the last date of his/her last RECIST assessment. PFS-derived data are based on assessment date rather than visit date.

Systemic PFS and iPFS will be assessed separately:

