## **4. Tumor Response Evaluation**

### **4.1 Evaluation plan**

CT examinations of the chest and abdomen (including the liver and adrenal glands) will be used to assess tumor burden at baseline and follow-up. CT with intravenous (IV) contrast is the preferred method. MRI should be used when CT is not feasible or medically contraindicated.

Baseline tumor assessment, which should be performed  $\leq 28$  days prior to start of study treatment, should involve all

regions in which diseases under assessment are known to metastasize, and potentially involved regions should be additionally assessed based on signs and symptoms of individual patients. Follow-up assessments should be performed every 6 weeks ( $\pm 7$  days) after the start of treatment until discontinuation of study treatment or withdrawal of informed consent. Imaging examination should also be performed at follow-up if new lesions are suspected at other sites.

If unscheduled assessments are performed and the patient has no progression, every effort should be made to enable the patient to perform subsequent assessments at the scheduled visits. This schedule will be followed in order to minimize any unintentional deviations due to the assessment of some patients at a follow-up frequency different from that for other patients.

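### Sections 11.4.2 and Appendix D 4.1 (and, secondarily, 7.5) end study participation or scanning before progression, against the protocol's own rule to scan to RECIST progression

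*Protocol*

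**What the plan says.** **The general rule.** Section 7.8.1 separates stopping treatment from leaving the study. It lists an adverse event among the reasons for stopping treatment and says of such a patient that he or she "is not withdrawn from the study and will complete subsequent follow-ups as scheduled". It adds that "patients who discontinue study treatment due to reasons other than PD should undergo tumor assessments as scheduled until documented PD", with an exemption for patients who leave the study for a reason under 7.8.2. The PFS definition in 12.1.2 agrees: for a patient who stops drug without progression, "his/her imaging tumor evaluation should still be collected until RECIST-defined PD". Section 6.1 (follow-up period), section 9.1.3.3, the tumor-assessment note to Appendix B and Appendix D 4.5 (symptomatic deterioration) say the same.

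**The departures.**
- Section 11.4.2, for treatment-related toxicity that persists or recurs after the second dose reduction has been considered: "the subject should be withdrawn from the study and should be followed up until the toxicity is recovered".
- Appendix D 4.1, on the period of follow-up scans: "after the start of treatment until discontinuation of study treatment or withdrawal of informed consent".
- Section 7.5: "If treatment has been started for a subject not meeting the eligibility criteria, the subject should be withdrawn from the study". The sentence before it leaves the decision on stopping treatment to the investigator's assessment.

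**How the data are used.** Under 12.1.2 a patient without progression or death is censored at the last RECIST assessment, and so is one whose progression or death follows two or more missed visits. The primary estimate is the Kaplan-Meier 12-month PFS rate (12.4.2.1), mainly in the full analysis set of all dosed patients (12.4.1). The hypotheses are 40% against 60% (5.3), with no control arm.

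**The concern.** Kaplan-Meier estimation treats a censored patient as having the same later risk as those still under observation. A patient who leaves because of drug toxicity, or because treatment has stopped, may not have that risk. If sites follow 11.4.2 or Appendix D 4.1 as written, such patients drop out of the risk set as non-events for a reason tied to treatment. There is no control arm in which a similar bias could offset this, because the estimate is compared with a fixed 40%.

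Scans that are never taken cannot be recovered at the analysis stage. With about 20 planned sites, two sets of instructions also invite different practice from site to site.

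**Working it through.** **1. The texts side by side**

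| Patient | General rule | Departing passage |
|---|---|---|
| Stops for toxicity, no progression | In study, scanned to progression (7.8.1, 9.1.3.3, 12.1.2, 6.1, Appendix B note) | 11.4.2: out of the study, followed until toxicity recovers |
| Stops treatment for any reason, no progression | As above; also Appendix D 4.5 | Appendix D 4.1: scans end when treatment ends |
| Ineligible but treated | In the full analysis set (12.4.1) | 7.5: out of the study |

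The study-withdrawal reasons in 7.8.2 are consent withdrawal, study termination or site closure, loss to follow-up and death. Toxicity and ineligibility are not named, but the list is open. A site that withdraws a patient under 11.4.2 can therefore read the exemption in 7.8.1 as ending scans. Section 7.8.2 allows survival status to be taken from public sources, but under 12.1.2 a death after two missed visits is still censored.

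**2. The plan's only figure on early loss.** Section 5.3 allows 20% dropout on 49 patients: 49/(1 − 0.20) = 61.25, rounded up to 62, against 63 stated. The allowance restores numbers; it does not remove bias from informative censoring.

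**3. Illustration of size.** These assumptions are not in the documents: exponential PFS with hazard λ on study; a constant rate δ of stopping without progression, with all such patients censored; hazard mλ afterwards. Censoring at stopping makes Kaplan-Meier estimate exp(−12λ). The true rate is

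S(12) = exp(−12(λ+δ)) + ∫₀¹² δ·exp(−(λ+δ)u)·exp(−mλ(12−u)) du.

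Example with 20% net stopping and m = 3: 12δ = −ln 0.80 = 0.2231. Take a Kaplan-Meier value of 0.446, so 12λ = 0.8074.
- First term: 0.446 × 0.80 = 0.3568.
- Second term: 0.2231 × 0.446³ × (e^1.3918 − 1)/1.3918 = 0.2231 × 0.0887 × 2.171 = 0.0430.
- Sum: 0.3998, so a true 40% is reported as 44.6%.

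Kaplan-Meier estimate when the true rate is 40%:

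| Net stopping by month 12 | m = 1 | m = 1.5 | m = 2 | m = 3 |
|---|---|---|---|---|
| 5% | 40.0% | 40.4% | 40.7% | 41.1% |
| 10% | 40.0% | 40.8% | 41.4% | 42.2% |
| 20% | 40.0% | 41.6% | 42.9% | 44.6% |

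These are net percentages, as if progression did not intervene. In the example, the share that actually stops before progression is (0.2231/1.0305) × (1 − 0.3568) = 0.139, about 9 of 63 patients.

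**4. Effect on the test.** I assumed 63 patients, a true rate of 40%, and success declared when the lower limit of a two-sided 90% log-log interval exceeds 40%. Simulated one-sided type I error is about 5-6% with full follow-up. With censoring it is about 6% (10% net, m = 2), 10% (20% net, m = 2) and 16% (20% net, m = 3).

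**The case against.** **The general rule is clear where it counts.** It stands in the PFS definition and in the notes to Appendix B, which 9.1 names as the overall follow-up schedule. Appendix D 4.1 looks like unadapted template text: it also gives a 6-week scan interval against 8 weeks elsewhere. The 11.4.2 sentence may be loose wording. Table 10 in the same section speaks of stopping treatment, and its note has patients who stop observed until toxicity resolves, without study withdrawal. This explains how the conflict arose but leaves it in place, because 7.8.1 gives study withdrawal a different consequence from stopping treatment.

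**The 11.4.2 path is narrow.** This stands. The passage applies late in the toxicity sequence, and most patients who stop without progression fall under 7.8.1. It also does not say that toxicity alone is followed. The 5-20% range describes all stopping without progression and would apply only if sites followed Appendix D 4.1 throughout.

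**The direction is not established.** This also stands. Section 7.7.2 permits other anti-tumor treatment after stopping for reasons other than progression, so losing aumolertinib does not by itself prove a higher later hazard.

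**Section 7.5 is a weaker case.** It concerns ineligibility, not toxicity, and 14.2 allows no eligibility exemptions, so numbers should be small. A reader might infer that it biases the rate in the same direction, or that it contradicts membership of the full analysis set. The documents support neither: no link to prognosis is given, and a withdrawn patient remains in the set with censored time. What it does is remove analysed patients from follow-up.

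**Conclusion.** The contradiction is real and bears on how the primary endpoint is ascertained. It is an internal inconsistency that should be fixed. Sections 11.4.2 and Appendix D 4.1 carry the point; 7.5 is secondary.

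The statistical consequence is conditional. For 5-20% net stopping and a later hazard 1 to 3 times that of patients who stay, the 12-month rate is overstated by 0 to about 4.6 points. The bias is zero at equal hazard and would reverse if the later hazard were lower. For the 11.4.2 path alone the fraction is unknown and should be smaller than that for all stopping.

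A reader might infer that the trial's 12-month rate will be inflated by several points. The documents do not support that: they give no expected number of withdrawals and no later hazard, and their prevailing instruction is to keep scanning.

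**What to change.** Reconcile the follow-up wording only.

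- **11.4.2 and 7.5:** state that these patients remain in progression follow-up (9.1.3.3) and survival follow-up (9.1.3.5) unless a 7.8.2 reason, such as withdrawal of consent, applies.
- **Appendix D 4.1:** in "until discontinuation of study treatment or withdrawal of informed consent", replace the part about discontinuation of study treatment by a reference to 9.1.3.3. The 6-week and 8-week intervals also need reconciling.

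Leave every rule on when treatment is reduced, interrupted or stopped as it is, including the investigator's decision in 7.5. In particular, the new sentence in 7.5 should not say that treatment is discontinued, since that would make stopping mandatory.

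The cost is three wording changes. The visits are already planned in 9.1.3.3 and 9.1.3.5, and the sample size is unaffected.
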